### Ethics

This study received NHS Health Research Authority approval, having been reviewed and given favorable opinion by Yorkshire & The Humber-South Yorkshire Research Ethics Committee (3rd December 2020). All participants have/will be provided with study information and will sign an informed consent form. Parental consent is required for the inclusion of participants under the age of 16, while agreement from each child will also be sought. Information about the study is provided to parents and children, and this information was adapted for use by younger children to help ensure that information about the study is accessible. Where parents have difficulties with reading and writing, we will provide study information in an alternative format (e.g., audio file). We will also provide translations of study documents and interpreter services to include families who do not speak English. Parents will have the right to withdraw their child from the pilot. We will abide by the General Data Protection Regulations (2018). All data will be stored securely on university servers. All data will be confidential, and it will not be possible to identify a child or any member of their family within any publication arising from this work. All incidents and near misses will be reported to the University of Warwick Health and Safety Department via the Accident, Incident, and Near Miss Reporting Form.

## Results

Figure 1 provides the participant flow diagram. Accrual to the pilot stage of this project opened on 6th August 2021 and is due to close on 31st May 2022. We aim to publish the results of this feasibility study and process evaluation in 2023.

## Discussion

In this protocol, we have summarized a feasibility study and process evaluation for MST adapted specifically for children at risk of criminal exploitation and their families. This is an important group of young people to safeguard and support. Our primary aim is to understand whether it is feasible to complete a pilot trial of MST for children at risk of criminal exploitation, within existing services in England. Our secondary aims are to understand the acceptability of MST for children at risk of criminal exploitation, as well as to understand factors that will facilitate or hinder the successful implementation of MST for children at risk of criminal exploitation, and how they can be successfully managed. In terms of the current study status (May 2022), we have completed the adaptations to the logic model (phase 1.1) and the pre-pilot interviews (phase 1.2). We are in the final month of accruing new participants to the study pilot and we will continue to follow-up with these families until April 2023 (phase 2.1). Finally, we are about to commence accrual to the process evaluation/post-treatment interviews (phase 2.2).

In conclusion, the results of this study will inform whether it is advisable to progress onto a definitive trial for this adaptation of MST for children at risk of criminal exploitation. These young people and families are under-researched and hard to engage. Therefore, the lessons learned during this study about recruiting and retaining these families in research will inform future work with this population. Findings about the adaptations made to this research, and to the intervention during the COVID-19 pandemic will also provide useful lessons to inform future research.

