### Study setting

This study is taking place within community-based settings in England. Sites are based in Birmingham, Sandwell, Yorkshire, and Nottingham, within existing MST services. Study sites have adopted a multi-agency approach to recruitment and invite referrals from social services, youth offending teams, child and adolescent mental health services, and education. The steps in the pathway for the pilot are as follows: families are informed about the screening process and if they do not opt-out, they are screened for eligibility to take part in MST for children at risk of criminal exploitation. Participants who meet these criteria are assigned to receive MST for children at risk of criminal exploitation and complete an initial baseline assessment within 4 weeks before starting MST treatment. MST for children at risk of criminal exploitation will last for up to 6 months, and an additional assessment period will occur at the mid-point of treatment (at 3 months, although sometimes shorter depending on the length of treatment), the end of treatment (approximately 6 months), and at 6-month follow-up. Young people, families, therapists, and key stakeholders will also be invited to take part in an interview as part of the process evaluation and our investigation of the acceptability and experience of treatment. Further information can be found in the participant flow diagram (Fig. 1).

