### Data collection

Our proposed primary and secondary outcome measures are outlined below. These were discussed and considered collaboratively with MST professionals, and further reviewed by participants who took part in our phase 1.2 interviews. Eligible participants complete outcome measures 4 weeks before the commencement of treatment, and then at up to 13 (mid-point), up to 26 (end of treatment), and 52 weeks (12-month–6-month follow-up) from treatment commencing.

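### The April 2023 end of follow-up does not leave room for the 52-week assessment of families who start treatment after 1 May 2022, although accrual runs to 31 May 2022

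*Protocol article*

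**What the plan says.** Four statements in the protocol article bear on the calendar.

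- **Accrual.** Results: "Accrual to the pilot stage of this project opened on 6th August 2021 and is due to close on 31st May 2022". The Abstract gives the same dates. The Discussion, written in May 2022, confirms that recruitment was still open: "We are in the final month of accruing new participants to the study pilot".
- **Start of treatment.** Study setting says that participants "complete an initial baseline assessment within 4 weeks before starting MST treatment". Treatment therefore starts after baseline, by up to 4 weeks.
- **Last assessment.** Data collection sets the assessments after baseline "then at up to 13 (mid-point), up to 26 (end of treatment), and 52 weeks", and the last of them is described as "52 weeks (12-month–6-month follow-up) from treatment commencing". The Abstract and Study setting instead describe it as a 6-month follow-up after the end of treatment. Study setting also says that "MST for children at risk of criminal exploitation will last for up to 6 months".
- **End of follow-up.** Discussion: "we will continue to follow-up with these families until April 2023".

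Under Progression criteria, green for the candidate outcome measures requires 95% of recruited participants to complete them at every occasion, with missing data below 5%. Green for retention is at least 80%. Where a criterion is amber or red, the team examines the likely causes and considers mitigation.

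**The concern.** Accrual closes at the end of May 2022 and the last visit comes a year after treatment starts, so the last visit cannot fall before the end of May 2023. The stated end of follow-up is at least a month earlier. If the calendar is followed as written, the latest recruits have no final assessment for a purely administrative reason.

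This matters because completion of measures is one of the results the study exists to estimate. The completion criterion counts recruited participants over all occasions and makes no exception for a visit that falls due after the study has ended. Families lost to the calendar would look the same in that count as families lost to poor engagement or burdensome measures. The within-group estimate at the final assessment would also lose its latest recruits.

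**Working it through.** **Inputs.** Accrual from 6 August 2021 to 31 May 2022 (Results). Lag from baseline to treatment of 0 to 28 days (Study setting). Last assessment at 52 weeks = 364 days from treatment start (Data collection). End of follow-up in April 2023 (Discussion), taken as 30 April 2023, the most generous reading. Sample of 50 families (Design, Phase 2).

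**Step 1: last visit on the 52-week clock.** Last visit = accrual close + lag + 364 days.

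- No lag: 31 May 2022 + 364 days = 30 May 2023, which is 30 days after 30 April 2023.
- 4-week lag: 31 May 2022 + 28 + 364 days = 27 June 2023, which is 58 days after.

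The stated April 2023 is not reproduced under either lag. From 31 May 2022 to 30 April 2023 is 334 days, so on that date the last recruit is at week 334/7 = 47.7, or (334 − 28)/7 = 43.7 with the lag.

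**Step 2: latest start that fits.** 30 April 2023 − 364 days = 1 May 2022. With a 4-week lag, baseline would have to be by 3 April 2022.

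**Step 3: the other clock, 6 months after treatment ends.** For a family recruited on 31 May 2022:

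| Treatment length | No lag | 4-week lag |
|---|---|---|
| 4 months | 31 March 2023, fits | 28 April 2023, fits |
| 5 months | 30 April 2023, just fits | 28 May 2023, does not fit |
| 6 months | 31 May 2023, does not fit | 28 June 2023, does not fit |

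In days, the room left for treatment is 334 − 182 = 152 (about 5 months), or 152 − 28 = 124 with the lag (about 4 months).

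**Step 4: how many families, on the 52-week clock.** The article gives no monthly counts, so I assume uniform accrual over the 299 days of the window, counting both end dates.

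- No lag: recruits of the last 30 days, 30/299 = 10.0%, or 5.0 of 50.
- 4-week lag: recruits of the last 58 days, 58/299 = 19.4%, or 9.7 of 50.

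**Step 5: effect on the criteria.** Green completion needs 0.95 × 50 = 47.5, so 48 families, and tolerates 2 incomplete. Losing 5 leaves 45/50 = 90% (amber). Losing about 10 leaves about 40/50 = 80%, the line between amber and red. The effect on the missing-data rate depends on its denominator, which the section does not give: 10% to 20% of the final visit, but 5/200 = 2.5% to 10/200 = 5% if all four occasions are pooled.

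**The case against.** The strongest reply is that the article carries two clocks. The Abstract and Study setting tie the last assessment to the end of treatment, and treatment length varies: the planned extension in Background is 4–6 months, and Study setting gives an upper limit only. On that clock, April 2023 suits a late recruit with a course of about 4 to 5 months. This stands. A reader might infer that every late recruit must lose the final assessment, and the article does not support that: the loss is certain only on the 52-week clock. The reply does not remove the conflict, because Data collection states 52 weeks from the start of treatment, and a full 6-month course overruns on either clock.

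The counts can also be challenged, and that stands too. Uniform accrual is assumed, 4 weeks is the maximum lag, and the article does not say whether accrual is dated at consent, baseline or treatment start. Reading the end of follow-up as 1 April would give larger losses, but that is the least generous reading and I do not rely on it.

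A reader might further infer that the study would fail its retention criterion or be stopped. Neither follows. Retention is not defined as attendance at the last visit, and even if it were, losing 10 of 50 leaves 80%, which is still green. An amber or red result leads to an examination of causes, which could well identify the calendar. That review would not recover the missed visits, however, and a denominator changed at that stage would be chosen after the results were seen.

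Finally, the April date appears once, in a status sentence, and may be a slip. It would then still need correcting.

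**Conclusion.** The point holds. Accrual to 31 May 2022, a 52-week visit and an end of follow-up in April 2023 cannot all be kept for families who start treatment after 1 May 2022. The shortfall for the last recruit is 30 to 58 days. This rests only on the stated dates, read generously.

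On the 6-months-after-treatment clock the loss is conditional: it affects the last recruits only when treatment exceeds about 5 months (about 4 with the lag).

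The figure of 5 to 10 families of 50 is an illustration under uniform accrual, a lag of 0 to 4 weeks and the 52-week clock. In that range the calendar alone moves all-occasions completion out of green. The effect on retention is uncertain because retention is not defined.

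**What to change.** First, state which clock defines the final assessment: 52 weeks from the start of treatment, or 6 months after treatment ends. Use it throughout the Abstract, Study setting and Data collection.

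Then choose one of two courses.

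1. Set the end of follow-up to the last treatment start plus 52 weeks, that is up to 27 June 2023. The cost is up to about two more months of follow-up contact.
2. If April 2023 is fixed, state now that families whose final visit falls due after that date are left out of the denominators for that visit's completion and missing-data rates, and are reported separately. The cost is a smaller sample at the final assessment, about 40 to 45 of 50 under the assumptions above.

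Either needs only a sentence or two in the article, and should be settled before the final assessments are in.

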## Data Availability

Once the study has been completed and the findings have been reported pilot data will be submitted to the Department for Education (UK). These data will then be anonymized and submitted to the Office for National Statistics Secure Research Service (UK). Once available, restrictions will apply to the access of these data to protect study participants. This process is in line with our funding requirements from the Youth Endowment Fund. Participants have consented to their data being used in this way.

## Abbreviations

MST: Multisystemic therapy
CCE: Child criminal exploitation
TAU: Treatment as usual
